##### 3) Integration of knowledge

The integration of knowledge into clinical decision-making is more complex than measures of utilization and, hence, more difficult to measure. However, as the ultimate purpose of new knowledge is to improve the quality of care, evaluation of how clinicians use new information to make decisions is critical. Simple measures of the use of concrete behaviors – prescription practices or completion of outcome scales – provide information on whether practitioners are receptive to changing their behavior. However, these measures do not provide insights about whether these altered clinical behaviors are integrated into higher-level clinical reasoning. As reviewed above, these higher-level evaluations are rarely incorporated into KT evaluations [63]. Chart-stimulated recall [75-77] is an evaluation method that combines personal interview and chart audit to engage participants in a reflective discussion on these deeper levels of cognitive reasoning. A trained evaluator draws inferences from the information to rate the clinician's behavior on a variety of items that reflect clinical reasoning and competency in the area of interest. This method was originally developed at McMaster University to evaluate competence in medical practitioners [76], and it has been shown to be a valid process in this population [75,76,78], as well as amongst occupational therapists [77].

The chart-stimulated recall form must be developed specifically for the competencies being evaluated. The competencies evaluated in this study will be the core curriculum about outcome measurements, with an emphasis on their application to clinical reasoning. This focus includes the clinician's ability to provide: a rationale for why specific outcome measures were selected for specific patients, an understanding of the correct application of the scale, an ability to use the obtained score to determine disability and prognosis, and the ability to set rehabilitation goals based on disability scores, including clear parameters for the expected change in scores following intervention. Chart-stimulated recall responses are scored on a seven-item scale that reflects the extent of competency [77]. The staged process of the study design will enable high-quality evaluations during chart-stimulated recall by allowing evaluators from Eastern and Western Canada to participate in Phase 1 of the project as a means of gaining greater consistency between raters.

The chart-stimulated recall will be conducted by a single trained research assistant assigned to each location. Two of the five charts selected for chart audit will be randomly selected for chart-stimulated recall. The interviewer will ask questions in a semi-structured format that requires specific responses from the therapist, explaining the content and clinical reasoning used for the two patients whose records are used to evaluate the core competencies being tested. The answers are scored on a seven-point scale. The spectrum of information included in the chart-stimulated recall analysis will include all intake assessments, progress notes, and discharge records for a specific patient. A detailed manual on the types of responses required will be developed in conjunction with curriculum development. Chart-stimulated recall will provide a quantitative assessment of the clinical reasoning used with respect to the use of outcome measures in managing specific patients.

## Analyses

### Quantitative analyses

All data will be double-entered in SPSS 14.0. Descriptive analyses will be conducted, including checking for outliers, normality testing, and univariate correlations. The first primary analysis (Objective 1) will be a two-way repeated measures analysis of variance to determine primary unadjusted differences in absolute scores over time, and between groups for each of the three primary outcome measures: knowledge, utilization, and chart-stimulated recall scores. An analysis of covariance will be used to compare these same effects adjusting for baseline knowledge score, Readiness to Change, years of practice, and educational preference. These analyses across the e-PBL and SHIPS groups will determine the relative effectiveness of these two alternative knowledge transfer choices. Effect sizes and their 95% confidence intervals will be calculated to determine whether there are differential impacts on change in knowledge, utilization, and integration of knowledge between the two different KT approaches. For the secondary research question (Objective 2.3) on the relative importance of KT predictors, a multiple linear regression [79,80] will be used to develop models of how years of practice, educational background, caseload characteristics, educational preferences, or Readiness to Change predict changes in knowledge, utilization, or integration following knowledge transfer interventions, with KT method as a covariate.

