**Method/Design:**

Physical and occupational therapists (n = 144) will be recruited in partnership with the national professional associations to evaluate two different KT interventions with the same curriculum: 1) Stakeholder-Hosted Interactive Problem-Based Seminar (SHIPS), and 2) Online Problem-Based course (e-PBL). SHIPS will consist of face-to-face problem-based learning (PBL) for 2 1/2 days with outcome measure developers as facilitators, using six problems generated in consultation with participants. The e-PBL will consist of a 6-week web-based course with six generic problems developed by content experts. SHIPS will be conducted in three urban centers in Canada. Participants will be block-allocated by a minimization procedure to either of the two interventions to minimize any prognostic differences. Trained evaluators at each site will conduct chart audits and chart-stimulated recall. Trained interviewers will conduct semi-structured interviews focused on identifying critical elements in KT and implementing practice changes. Interviews will be transcribed verbatim. Baseline predictors including demographics, knowledge, attitudes/barriers regarding outcome measures, and Readiness to Change will be assessed by self-report. Immediately post-intervention and 6 months later, these will be re-administered. Primary qualitative and quantitative evaluations will be conducted 6-months post-intervention to assess the relative effectiveness of KT interventions and to identify elements that contribute to changing clinical behavior. Chart audits will determine the utilization of outcome measures (counts). Incorporation of outcome measures into clinical reasoning will be assessed using an innovative technique: chart-stimulated recall.

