### Study measures

#### Baseline measurement of eligibility, status, and potential KT predictors

Participants will be pre-screened to ensure inclusion criteria. Eligible participants will then complete a baseline knowledge pre-test (to avoid ceiling effects/lack of responsiveness). Participants also will complete a baseline information questionnaire to collect demographic data, practice patterns, and educational background. Survey measures of knowledge and behavior will be administered. This data collection also will include a measurement of the therapist's intent to use outcome measures, their general level of research utilization, and their readiness to change. This scale evaluating Readiness to Change [40,41,73] was developed to reflect the core elements of the five stages of change, but was specifically applied to changing clinical practice. Although all participants will have agreed to allocation during informed consent, they will be asked their preference with respect to e-PBL and SHIPS so that post-hoc analyses can determine the importance of educational preference as a mediator of response.

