##### 2) Utilization

Chart audit will be used to measure utilization of outcome measures. In many situations, chart audit does not accurately represent the content of a clinical interaction because not all information is recorded [74]. However, in our case the reverse is true. Specific self-report forms are required to administer outcome measures and will provide direct evidence of utilization. Charts will be selected for a chart audit procedure as follows: a) one day from each participant's previous month of practice will be selected randomly, b) a list of patients seen on that day will be generated, and c) five patient charts will be selected randomly from that daily list. Using a standardized data extraction form, the entire chart record will be audited to determine the total numbers of outcome measures used, the frequency of use, the timing of use (i.e., every session, at evaluation and discharge), and the specific outcome measures used. In addition, it will be recorded whether scales were scored correctly, and whether the scales were specifically mentioned in goal setting or discharge planning.

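### Utilization and chart-stimulated recall have no stated baseline, yet their planned primary analysis is a repeated-measures ANOVA over time and their conclusions are about change

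*Protocol article*

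**What the plan says.** **Analysis.** Quantitative analyses (Objective 1) specifies "a two-way repeated measures analysis of variance to determine primary unadjusted differences in absolute scores over time, and between groups", to be run "for each of the three primary outcome measures: knowledge, utilization, and chart-stimulated recall scores". An analysis of covariance then looks at the same effects "adjusting for baseline knowledge score, Readiness to Change, years of practice, and educational preference". Effect sizes with 95% confidence intervals are to show "differential impacts on change in knowledge, utilization, and integration of knowledge between the two different KT approaches". For Objective 2.3, multiple linear regressions are to "predict changes in knowledge, utilization, or integration following knowledge transfer interventions".

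**Schedule.** The section on baseline measurement lists the knowledge pre-test, a background questionnaire, intent to use outcome measures, general research utilization, Readiness to Change and preferred delivery mode. On behavior it says "Survey measures of knowledge and behavior will be administered". It mentions neither chart audit nor chart-stimulated recall.

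Both are described under the heading for post-intervention evaluations: "Chart audit will be used to measure utilization of outcome measures", with recall conducted on two of the five audited charts. In that part of the article a baseline is named for knowledge alone, namely the screening test.

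The Abstract (Method/Design) agrees. The baseline set is self-reported and is repeated immediately after the intervention and 6 months later. It then says "Primary qualitative and quantitative evaluations will be conducted 6-months post-intervention to assess the relative effectiveness of KT interventions".

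**The concern.** A two-way repeated-measures ANOVA with time as a factor needs at least two measurements of the same quantity on each therapist. Knowledge has them. For utilization and recall the article describes none before the intervention.

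These two are the behavioral outcomes, and Objective 1 asks about changing all three. If the data arrive on the stated schedule, the analyst will find that the named primary model does not fit the data for two outcomes and will have to choose a substitute after the fact. The likely result is a 6-month difference between arms reported as a difference in change.

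That wording matters more than usual here, because allocation is by a matching and minimization procedure that the article itself calls non-randomized. Prior use of outcome measures and prior clinical reasoning are not among the factors it balances.

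**Working it through.** **1. Schedule against analysis, by outcome**

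| Outcome | Baseline stated? | Follow-up stated | Baseline value in ANCOVA? | Time, interaction and change computable? |
|---|---|---|---|---|
| Knowledge | Yes, screening test | Immediately after and 6 months | Yes | Yes |
| Utilization (chart audit) | No | Primary evaluation at 6 months | No | No |
| Chart-stimulated recall | No | As the audit (two of the five audited charts) | No | No |

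With a single occasion, the group-by-time model reduces to its group term, that is, a two-sample comparison. Two of three primary analyses and two of three Objective 2.3 responses are affected.

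**2. Could something else serve as the first occasion?**

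- The baseline behavior survey is self-report, while the outcome is an audit count. Using one as time 1 and the other as time 2 would confound instrument with time. No survey counterpart of the recall score is described.
- The audit reads the whole chart, so some entries may predate the intervention. But the charts come from patients seen on one day in the previous month, which gives no comparable pre-intervention sample for each therapist.

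**3. What the planned sample size supports**

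Inputs from Sample size requirements: two-sided alpha 0.05, effect 0.50 SD between groups, 10% dropout, and 0.80 (printed as Type II error; 64 per group is obtained only if it is read as power).

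- Normal approximation: n = 2 × (1.960 + 0.842)² / 0.50² = 62.8, so 63 per group.
- Two-sample t-test: 63.77, so 64 per group. This is the stated figure.
- Dropout: 128 / 0.9 = 142.2, stated as 142 and rounded up to 144.

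The plan's figure is therefore the size for a two-group comparison at one time point, with no within-person correlation in it. At 64 per group the power of that comparison is 0.80.

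**4. If a baseline round exists**

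The within-person correlation ρ is not in the article; 0.3 to 0.7 is assumed. With the effect at 0.50 SD and two-sided alpha 0.05:

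- ANCOVA on the baseline score: n = 63.77 × (1 − ρ²)
- Group-by-time interaction with two occasions (equivalent to a change-score test): n = 63.77 × 2(1 − ρ)

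| ρ | ANCOVA: n per group | ANCOVA: power at 64 | Interaction: n per group | Interaction: power at 64 |
|---|---|---|---|---|
| 0.3 | 59 | 0.84 | 90 | 0.66 |
| 0.5 | 48 | 0.90 | 64 | 0.80 |
| 0.7 | 33 | 0.98 | 39 | 0.95 |

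If a baseline is collected, using it as a covariate needs no more than the planned number anywhere in this range. The interaction test would need more than planned when ρ is below 0.5.

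**The case against.** The strongest reply is that post-only timing is inferred. The article nowhere says that there is a single audit occasion. The heading for post-intervention evaluations also covers knowledge, which does have a pre-test. The baseline section is framed around eligibility, status and predictors, so it may not be a full list of outcome occasions. The analysis section and Objective 1 can themselves be read as signs that repeated measurement is meant, and a condensed article may leave the visit schedule to the full protocol.

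This stands as a limit on certainty. It does not remove the conflict: the baseline lists are detailed, knowledge alone is given a baseline, and the ANCOVA omits the covariates that a baseline round would supply. If such a round is planned, the schedule and the ANCOVA both need correcting.

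Three stronger readings are tempting, and the documents do not support them:

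- *The two outcomes cannot be analysed at all.* The between-arm contrast at 6 months and its covariate-adjusted version remain computable. Only the time, interaction and change parts fail.
- *There is no protection against prior differences in use.* Allocation is done within orthopedic and pediatric groups at each site, and the Background says that utilization differs between these fields. Therapists are also paired on profession, practice area, pre-test score and years of practice, and the ANCOVA includes Readiness to Change. The protection is indirect and incomplete, but it exists.
- *Chance imbalance in prior use adds a quantifiable error to the 6-month result.* A figure such as 1.96 × √(2/64) = 0.35 SD describes simple randomization, not matched allocation within strata. It is also the half-width that the confidence interval of a 6-month comparison already carries, so counting it again would be double counting.

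**Conclusion.** The concern holds as a conflict between the stated measurement schedule and the stated analysis. On the schedule as written, the time effect, the group-by-time interaction and the change scores cannot be computed for utilization and chart-stimulated recall. That affects two of three primary outcomes and two of three predictor regressions. What can be computed is a 6-month between-arm comparison, which has power 0.80 at 64 per group on the plan's own assumptions (0.50 SD, independent therapists).

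The conclusion assumes that the listed baseline measures are the ones taken. A reader might infer that the article rules out a baseline audit. It does not; it only fails to list one while relying on one in the analysis. The conclusion does not depend on any assumed correlation. The range for ρ bears only on the choice of analysis if a baseline round exists.

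**What to change.** Reconcile the baseline and post-intervention measurement sections with Quantitative analyses by stating whether a chart audit and recall take place before the intervention.

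**If they do not:**
- Make the primary analysis of utilization and of recall a between-arm comparison of the 6-month score, adjusted for the baseline self-reported behavior and intent already collected plus the planned covariates.
- Use the 6-month level as the response in the Objective 2.3 regressions for these two outcomes.
- Word the conclusion as a 6-month difference between arms, and keep the language of change for knowledge.

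This costs rewording only; the 64 per group is unaffected and no new data are needed. The real price is that Objective 1 is then answered for these two outcomes as a difference in level, which should be said openly.

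**If they do:** state the baseline round with the same chart-sampling rule, and add baseline utilization and baseline recall score as covariates in the ANCOVA. This costs a sentence on the schedule and two covariates.

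Rebuilding a baseline later from chart entries dated before the intervention is not a substitute. Those records would be cut off at one occasion and complete at the other, so the two counts would not be comparable.

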#### Sample size requirements

Given that this study is a mixed-methods design, the sample size was based on the quantitative analyses as these have larger sample size requirements. Sample size estimation was based on detecting an effect of 0.50 between groups on any of the three aspects of outcome (knowledge, utilization, and integration into clinical reasoning). Assuming Type I error = 0.05 (2-tailed); Type II error = 0.80; Effect size = 0.50, the sample size required per group = 64. The sample size required for two-comparison groups = 128 and accounting for a 10% dropout = 128/0.9 = 142. We anticipate low dropouts given the priority of continuing education by both professions. We will round our sample size up to 144 to provide a number equally divided between three sites, requiring 48 per site. Based on the need to allocate participants in blocks to interventions and to balance professions and clinical areas evenly, we expect to accommodate 24 participants per intervention group, per site. These will consist of three tutorial groups of eight therapists/groups. Given the distribution of practice patterns in rehabilitation, we expect two groups on orthopedics and one group on pediatric practice at each location. Groups will be formed according to practice settings to insure that the stakeholders can develop "problems" that simulate their own clinical settings/populations.

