#### Group assignment procedure

A randomized design is usually the most rigorous, allowing for control of known and unknown confounders. In this case, it is not the most appropriate design strategy and we have selected a quasi-experimental approach. Research design methodologists have indicated that attaining an equal distribution of confounders in small samples via randomization, such as that required for the present study, is unreliable. Therefore we will use a non-randomized allocation procedure called minimization, which places participants in intervention groups to minimize the differences across key predictors [69-71]. We have identified pre-test scores, years of practice, practice area (urban/rural), and practice type (PT/OT) as the key predictors. Minimization across key predictors will balance prognostic variables and result in more valid comparisons [71]. Subjects will be allocated using minimization within orthopedic and pediatric groups at each site. At each site the pool of subjects will be allocated minimizing difference by: creating pair groupings based on professional training (PT/OT), matching area practice and then most similar pre-test scores, and, finally, by minimizing years of practice. We then will conduct descriptive analyses of group similarities and test whether we can optimize groups' consistency by reallocation of assignment. When this process is complete, subjects at each site will be informed of their assignment.

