#### Post-intervention evaluations of KT impact

##### 1) Knowledge

The screening multiple-choice test will form the baseline knowledge score. Alternate forms of this test will be devised for pediatric and musculoskeletal populations; test content will be mapped to the curriculum objectives. A bank of questions reflecting the key knowledge curriculum will be developed, and participants will be provided with alternate forms for pre- and post-test evaluations to minimize recall bias as a potential reason for score inflation.

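### The primary repeated-measures ANOVA does not fit the measurements described, leaves its deciding term open, and omits most of the allocation factors

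*Protocol article*

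**What the plan says.** **Analysis.** Quantitative analyses names a two-way repeated-measures ANOVA as the first primary analysis for Objective 1, "to determine primary unadjusted differences in absolute scores over time, and between groups for each of the three primary outcome measures". The three are the knowledge test, chart-audit utilization and chart-stimulated recall. An ANCOVA of the same effects follows, "adjusting for baseline knowledge score, Readiness to Change, years of practice, and educational preference". The section then promises effect sizes for differential change in all three outcomes, and a regression of changes in all three.

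**Measurement.** The abstract says "Primary qualitative and quantitative evaluations will be conducted 6-months post-intervention". The baseline section lists the knowledge pre-test, a background questionnaire, intent, research utilization, Readiness to Change and educational preference, and adds "Survey measures of knowledge and behavior will be administered". Chart audit and chart-stimulated recall are described only under the post-intervention heading. Knowledge sits under that heading too, but there the screening test is expressly named as its baseline.

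**Allocation.** Group assignment procedure says "Subjects will be allocated using minimization within orthopedic and pediatric groups at each site". The key predictors it names are pre-test score, years of practice, practice area (urban/rural) and practice type (PT/OT).

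**The concern.** A repeated-measures ANOVA needs at least two measurements of the same variable. As described, utilization by chart audit and clinical reasoning by recall have one. If no baseline is taken, the named primary test has no time factor for two of the three primary outcomes. If one is intended, the article does not describe it, and a pre-intervention recall interview that was not held cannot be recovered later.

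For knowledge, the ANOVA yields a group main effect, a time effect and a group-by-time interaction. The main effect averages in the baseline, where allocation makes the arms alike. The interaction tests differential change. Neither is simply the 6-month contrast, and the plan does not choose between them.

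The factors used to form balanced groups are also mostly absent from the models. The article itself gives reasons to expect some of them to explain variance. Its Background reports higher utilization in pediatric practice. On the knowledge test it says "Alternate forms of this test will be devised for pediatric and musculoskeletal populations". Each location has a single recall assessor.

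**Working it through.** **1. Reproduce the plan's figure.** Sample size requirements gives "Assuming Type I error = 0.05 (2-tailed"), "Type II error = 0.80" and an effect size of 0.50, hence 64 per group. The second figure must mean power, since only power of 0.80 gives 64. A two-sided two-sample t-test at d = 0.50 has power 0.795 with 63 per group and 0.8015 with 64. Then 2 × 64 = 128 and 128/0.9 = 142.2, taken up to 144. So 64 reproduces, but as a single-time-point comparison, not as the ANOVA named for the primary analysis.

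**2. Baselines, outcome by outcome.**

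| Outcome | Baseline on the same instrument | Analysis asks for |
|---|---|---|
| Knowledge | Yes, the screening test | Scores over time, change |
| Utilization (chart audit) | None described; a behavior survey is | Scores over time, change |
| Integration (recall) | None described | Scores over time, change |

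**3. Power by deciding term.** Inputs: 64 per arm and a 0.50 SD difference (from the document); no baseline difference, equal variances and a common correlation r between time points (assumed 0.3, 0.5, 0.7, as none is given). For three time points, the 0.50 difference is assumed at both post-intervention times. Each term has a mean difference and a variance in SD units; the standardized effect is difference/√variance, put into the noncentral t.

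- Group main effect, three time points: difference (0 + 0.5 + 0.5)/3 = 0.333, variance (1 + 2r)/3.
- Group main effect, baseline and 6 months: difference 0.25, variance (1 + r)/2.
- Interaction, two time points: difference 0.5, variance 2(1 − r).
- ANCOVA of the 6-month score on its own baseline: difference 0.5, variance 1 − r².

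Example at r = 0.5: the three-time-point main effect is 0.333/√0.667 = 0.41; ANCOVA is 0.5/√0.75 = 0.58.

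| Term | r = 0.3 | r = 0.5 | r = 0.7 |
|---|---|---|---|
| Main effect, three time points | 73% | 63% | 55% |
| Main effect, two time points | 41% | 37% | 33% |
| Interaction, two time points | 66% | 80% | 95% |
| Interaction, three time points (2 df) | 69% | 84% | 97% |
| ANCOVA at 6 months | 84% | 90% | 98% |

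**4. Allocation factors left out.** Suppose balanced but omitted factors explain a share R² of outcome variance (assumed 10%, 20%, 30%). The unadjusted standard error is then too large by 1/√(1 − R²). With z = 0.5 × √32 = 2.83 and Φ the normal distribution function:

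- True size of the nominal 5% test: 2 × [1 − Φ(1.96/√(1 − R²))]
- Unadjusted power: Φ((2.83 − 1.96)/√(1 − R²))
- Adjusted power: Φ(2.83/√(1 − R²) − 1.96)

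| R² | True size | Power, unadjusted | Power, adjusted |
|---|---|---|---|
| 10% | 3.9% | 82% | 85% |
| 20% | 2.8% | 83% | 89% |
| 30% | 1.9% | 85% | 92% |

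**5. Which factors are missing.** The ANCOVA covers pre-test score and years of practice, two of the four named predictors. Practice area, profession, site and orthopedic/pediatric stratum are in neither model.

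**The case against.** **Missing baselines.** This is a condensed article, and silence is not proof. Knowledge is under the same post-intervention heading and has a baseline, and the talk of change suggests that baseline audits and recall may be intended. A reader might infer that the primary test cannot be computed for two outcomes. The document does not support that; it supports only that none is described while the analysis needs one. The conflict stands.

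**Dilution.** A reader might infer that the planned test averages the effect with baseline and so falls to 63% power at r = 0.5. That is true only of the group main effect. The stated interest in differential change may point to the interaction, where the shortfall against ANCOVA is 6 points or fewer in the three-time-point case once r reaches 0.5. It is about 15 points at r = 0.3. What stands is that the choice is not made.

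**Allocation factors.** The omission is conservative, and on the figures above the unadjusted test keeps more than the planned 80% power. Different tests by population, different utilization levels and one assessor per site fall on both arms alike, because allocation is within site and stratum. A claim of bias would therefore be wrong. This part concerns precision.

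**The existing ANCOVA.** It already adjusts knowledge for its own baseline. But it accompanies an analysis labelled primary and unadjusted, and it carries no baseline for the other two outcomes. If those outcomes have no baseline, that last point is no fault of the ANCOVA.

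**Conclusion.** The concern holds in this form. The primary analysis presupposes repeated measurement of three outcomes, while the article describes it for one. This is a contradiction to reconcile, not proof that baselines are absent. The deciding ANOVA term is not fixed. Depending on the term, the number of time points and r (0.3-0.7), power at 64 per arm runs from 33% to 97%, against 84-98% for a baseline-adjusted 6-month comparison. Four allocation factors are in neither model. If they explain 10-30% of variance, true size is about 2-4% and about 3-7 points of power are given away, without bias. Both r and R² are assumptions. The ANCOVA figures apply only to an outcome with its own baseline, which on the present text means knowledge. The calculations treat therapists as independent, as the plan's sample size does.

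**What to change.** - Define the primary analysis, for each outcome, as the SHIPS minus e-PBL difference at 6 months. Adjust for site, orthopedic/pediatric stratum, profession, practice area, pre-test score and years of practice, plus the outcome's own baseline where one is measured. For knowledge, that baseline is the pre-test.
- For utilization and recall, choose one course and align the sections. Either state that a baseline audit and recall are done and adjust for them, or compare 6-month scores only and remove the wording about scores over time and change, including in the predictor regression.
- Do not assume that a utilization baseline can be rebuilt from older chart entries. Charts are drawn from patients seen on one day in the previous month, and many may not have been patients before the intervention. The baseline behavior survey is not the chart-audit outcome either.
- Keep the repeated-measures ANOVA as a secondary description of knowledge over time.

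The allocation factors are recorded in order to allocate, so adjusting for them costs wording and a few degrees of freedom. Baseline audits and recall, if chosen and not already planned, would add fieldwork before the intervention.
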